After completion of the trial details of which combination above was prescribed will be added to the patient notes.

## Study setting

The study will take place entirely at DMRC Headley Court. This is the MOD’s tertiary referral centre for Sport Exercise and Rehabilitation Medicine. Patients are referred to Headley Court as part of routine care.

### Recruitment

RRU doctors have been briefed and provided with additional information to have an awareness of this trial and may suggest referral to DMRC Headley Court once the physical therapies in the current guidelines and ESWT have been tried without success. They may mention that a trial is taking place.

### Patient identification

The trial will be mentioned by RRU staff to potential participants and further information will be provided. Once a referral has been made the patient will be sent written information and a copy of the consent form so that they have a minimum of 24 h to consider the information before attending DMRC. It will be stressed that if patients do not wish to participate in the trial they will not be prejudiced and will be treated in line with current best practice. They will still be welcomed to attend DMRC appointments.

### Screening

Patients will be screened as per their normal routine care for a tertiary referral to DMRC Headley Court. They will have a 45-min initial appointment with one of the research team consultants. This will include reviewing their medical history and checking parameters such as weight, BMI, pulse and blood pressure. No more invasive tests are required.

### Withdrawal criteria

In accordance with the Declaration of Helsinki participants will be free to withdraw at any time. This trial requires that a single injection only is delivered on the day of consenting to the trial. Compliance and drop out in this respect is therefore not anticipated to be a problem.

It is possible that participants may perceive having to travel and attend follow-up appointments an inconvenience. Under those circumstances further options for gaining follow up data include its collection at RRU and failing that primary outcome measures could be assessed remotely.

Should the participant no longer wish to participate in the physical elements of the rehabilitation, which is current standard practice they are of course free to do so. A 10% drop out rate has been allowed for (see below).

### Sample size

The effect size *f* has been calculated along with the overall predicted sample size calculation using GPower (University of Dusseldorf, GER) [33]. The Minimum Clinically Important Difference (MCID) in the VISA-P score in athletes with patellar tendinopathy who underwent conservative management was calculated by Hernandez-Sanchez [34] to be 12.6 (*n* = 90 baseline VISA-P = 50.1 (SD = 18.4). The effect size *f* of 0.3228096 was combined with an α-level of 0.05 and power of 0.8 in a priori power calculation for an ANOVA, fixed effects, omnibus one way test predicting an initial sample size of 96. The calculation was repeated so that addition of a suspected covariate (percentage adherence to the standardised rehabilitation protocol) could be considered in ANCOVA again a sample size of 96 was predicted. Further calculations were made to allow using repeated measures, between factors ANOVA assuming correlation of 0.5 among repeated measures this returned a smaller total sample sizes of 75 for primary outcome measures (baseline and 6 month follow-up) and 60 for secondary outcome measures (baseline, 6 weeks, 3,6 and 12 month follow-ups). 108 participants with either Achilles or patellar tendinopathy will be recruited to allow for a 10% drop out rate.

### Statistical analyses

Demographic data over the 3 RCT groups will be compared. This will include the risk factors to be analysed as part of a correlational study including age, obesity, smoking, blood group, hypertension and family history. Parametric assumption checks will be made and one-way ANOVA used to check for statistical differences that may have occurred by chance at baseline. Where necessary ANCOVA will be used to correct differences across the groups. The adherence to rehabilitation score will be considered as a covariate.

The primary outcome data will be compared between groups at baseline and 6 months. Individual outcome measures for each group will be analysed to check parametric assumptions. For primary and secondary outcome measures a repeated measures, between factors ANOVA (time x intervention) will be used to look for significant difference. Groups will then be compared against each other using *post hoc* pairwise comparisons using SPSS software and effect sizes calculated.

A protocol deviation log is to be kept so that unanticipated trends can be analysed. The proportion of missing data will be reported with reasons where possible. Missing data will be handled using multiple imputation calculated in SPSS. A minimum of 5 imputations will be used. Results for completed cases will be compared to those based on multiple imputation and reported in accordance with the guidance proposed by Sterne et al. [35].

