### Follow up

Outcome measures will be taken at baseline and at 6 weeks and 3, 6 and 12 months follow up.

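### Multi-visit secondary outcomes: the repeated measures ANOVA fixes neither a sphericity correction nor a covariance model, so an uncorrected 5% test could run anywhere from about 5% to 9%

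*Protocol article*

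**What the plan says.** The analysis model is stated in Statistical analyses: "For primary and secondary outcome measures a repeated measures, between factors ANOVA (time x intervention) will be used to look for significant difference". Pairwise comparisons between arms follow. The same section limits the primary comparison to baseline and 6 months.

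The schedule comes from the Follow up section: "Outcome measures will be taken at baseline and at 6 weeks and 3, 6 and 12 months follow up". According to the list of secondary endpoints and Table 5, VAS, VISA and FAA are recorded at all five visits. The ultrasound, strength and small knee bend measures are recorded at the four visits up to 6 months.

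On assumptions, the article says: "Individual outcome measures for each group will be analysed to check parametric assumptions". It does not list which assumptions are meant, and it does not say what follows if one fails.

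The Sample size section includes a repeated-measures calculation "assuming correlation of 0.5 among repeated measures", giving 75 participants for two time points and 60 for five. The recruitment target rests on the larger one-way figure of 96.

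**The concern.** With three or more visits, the univariate time-by-intervention F test assumes sphericity: the difference between any two visits has the same variance whichever pair is taken. Here the gaps run from about six weeks to twelve months. Repeated scores from the same person usually correlate less as the gap widens, and that breaks the assumption. The uncorrected test then rejects too often when there is no effect.

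As worded, the planned check looks at each measure within each group. The relevant quantity is the covariance between visits. The article also leaves open which p-value decides (uncorrected, Greenhouse-Geisser or another), so that choice could be made after the data are seen.

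At stake are the secondary results over time, including the 12-month VAS, VISA and FAA, which are the longest follow-up in the trial. The error goes in one direction, towards false signals of a difference between arms.

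**Working it through.** **1. What the 0.5 is used for.** The Sample size section gives an MCID and SD ("to be 12.6 (*n* = 90 baseline VISA-P = 50.1 (SD = 18.4") and an effect size "of 0.3228096 was combined with an α-level of 0.05".
- Effect size: f = (12.6/18.4) × √2/3 = 0.3228, one arm differing by the MCID from two equal arms. f² = 0.1042.
- One-way ANOVA: λ = f²N = 0.1042 × 96 = 10.00 on 2 and 93 df, power 0.802. This reproduces the stated 96.
- Repeated measures, between factors, with m time points: λ = f²N·m/(1 + (m − 1)ρ), ρ = 0.5, on 2 and N − 3 df.
  - m = 2, N = 75: λ = 0.1042 × 75 × 2/1.5 = 10.42, power 0.815.
  - m = 5, N = 60: λ = 0.1042 × 60 × 5/3 = 10.42, power 0.811.

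All the figures reproduce. The 0.5 enters only the test of the group main effect (2 numerator df), whose type I error does not depend on sphericity.

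**2. The test at issue.** With 3 arms, N = 96 and m visits, the time-by-intervention F has (3 − 1)(m − 1) and (96 − 3)(m − 1) df. That is 8 and 372 for five visits (critical value 1.963) and 6 and 279 for four. Departure from sphericity is measured by ε = tr(T)²/[(m − 1)·tr(T²)], where T is the double-centred covariance matrix of the visits. ε = 1 means sphericity holds. Greenhouse-Geisser multiplies both df by the estimated ε.

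**3. Simulation under no effect.** Normal data, 3 × 32, visits at 0, 1.4, 3, 6 and 12 months, 60,000 runs per pattern (Monte Carlo SE about 0.1 point). The article gives no correlation by lag, so every pattern is an assumption. L is the lag in months.

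| Five visits: assumed correlation | ε | Uncorrected | Greenhouse-Geisser |
|---|---|---|---|
| Common 0.5 | 1.00 | 5.1% | 4.7% |
| 0.4 + 0.2·exp(−L/4) | 0.98 | 5.3% | 4.8% |
| Common 0.5, SD ratio rising 0.8 to 1.3 | 0.94 | 5.4% | 4.7% |
| Linear, 0.65 − 0.3·L/12 | 0.92 | 5.4% | 4.7% |
| 0.3 + 0.45·exp(−L/4) | 0.91 | 5.7% | 4.8% |
| AR(1) by visit, 0.5 | 0.81 | 6.5% | 4.9% |
| Linear, 0.8 − 0.5·L/12 | 0.77 | 6.9% | 5.0% |
| AR(1) by visit, 0.7 | 0.69 | 7.5% | 4.9% |
| Exponential decay, 6-month correlation 0.3 | 0.72 | 7.5% | 5.0% |
| Exponential decay, 6-month correlation 0.5 | 0.63 | 8.1% | 5.0% |
| AR(1) by visit, 0.8 | 0.63 | 8.1% | 5.0% |
| Exponential decay, 6-month correlation 0.7 | 0.57 | 9.0% | 5.0% |

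An analytic check agrees. Referring 1.963 to an F with df 8ε and 372ε at ε = 0.631 gives 8.4%, against 8.1% simulated.

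**4. Four visits (0 to 6 months).** Uncorrected: 7.3% (exponential, 6-month correlation 0.5), 6.5% (AR(1), 0.7) and 5.5% (linear, 0.8 − 0.5·L/12). Corrected: 4.7% to 5.0%.

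**5. Two visits (the primary comparison).** There is only one between-visit difference, so ε = 1 by construction. The simulated error is 5.0% with equal or unequal SDs.

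**The case against.** The strongest reply is that this is silence, not a mistake. The article never says the F test will be read uncorrected. It plans checks of parametric assumptions without listing them, and sphericity is one of those assumptions for this model. A correction rule commonly sits in the statistical analysis plan, which is not shown, and the corrected output is standard in the named software. This largely stands: the missing correction is not in itself an error. What remains is that the article does name a model whose validity depends on the between-visit covariance, and a better-behaved choice is available at almost no cost.

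Three stronger readings are tempting and not supported.
- A reader might infer that the test does run at 7% to 9%. That needs both no correction and a steep fall in correlation. Milder patterns give 5.3% to 5.7%.
- A reader might infer that the planned analysis assumes a common correlation of 0.5. That value is only an input to a between-groups sample size, and the recruitment target does not rest on it.
- A reader might infer that participants with a missed visit are lost. Multiple imputation is planned, and the complete-case result is only a comparison beside it.

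**Conclusion.** The point holds as a minor one, for the secondary outcomes measured at four or five visits. If the time-by-intervention F is used uncorrected, its actual type I error at a nominal 5% is about 5% to 9%. The low end applies when correlation is nearly constant over time, and the high end when it decays steeply towards zero. The size rests on assumed correlation patterns, normal data and 32 per arm. The article's own figures do not place the trial within that range. The primary comparison at 6 months and the sample size are untouched.

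**What to change.** Add one sentence to Statistical analyses. For outcomes with more than two visits, fit a linear mixed model with visit, intervention and their interaction and an unstructured covariance between visits. If the repeated measures ANOVA is kept, report Greenhouse-Geisser-corrected p-values in every case, rather than only after a significant sphericity test. Either is enough: in the simulations above the correction alone brought the error to between 4.7% and 5.0%. The mixed model has the further convenience that its estimates and standard errors pool directly over the planned imputations.

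Both options are standard in the named software. The cost is slightly lower power than the uncorrected test if sphericity does hold. The unstructured model must also estimate 5 × 6/2 = 15 variances and covariances at five visits.

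### The planned time-by-intervention ANOVA is valid but less efficient than an always-fitted baseline ANCOVA, and the quoted sample sizes of 75 and 60 belong to a different test

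*Protocol article*

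**What the plan says.** Protocol article, Statistical analyses: for primary and secondary outcomes "a repeated measures, between factors ANOVA (time x intervention) will be used to look for significant difference", followed by pairwise comparisons. The primary outcomes are compared at baseline and 6 months, so baseline is a level of the time factor and not a covariate.

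The same section has "one-way ANOVA used to check for statistical differences that may have occurred by chance at baseline", and then "Where necessary ANCOVA will be used to correct differences across the groups". Adjustment is therefore conditional. The covariate named there and in the sample size section is adherence to rehabilitation; the baseline outcome score is not fixed as a covariate anywhere.

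Protocol article, Sample size: an effect size f "of 0.3228096 was combined with an α-level of 0.05" and power of 0.8, for an "ANOVA, fixed effects, omnibus one way test predicting an initial sample size of 96". A further repeated-measures, between-factors calculation assumed a correlation of 0.5, and "this returned a smaller total sample sizes of 75 for primary outcome measures (baseline and 6 month follow-up"), with 60 for the secondary outcomes over five visits. The recruitment target is 108, which allows 10% dropout from 96.

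**The concern.** There are two linked problems.

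- **Efficiency.** Treating baseline as an outcome level makes the two-visit interaction a change-score analysis. When the correlation between visits is moderate, subtracting the whole baseline score adds noise that regression on baseline would remove. The trial already collects that score. ANCOVA enters only after a baseline test, and in a randomised trial such a test says nothing about which covariates predict outcome. It also leaves the form of the model dependent on the data.
- **Mismatched sample sizes.** The 75 and 60 are presented as sufficient for the repeated-measures analysis, but they appear to come from a test other than the interaction named in the analysis section. Under Blinding and data access, the trial may be declared complete short of its powered number if participants are lacking. In that event a published 75 for the primary outcomes could be taken as enough.

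**Working it through.** **Inputs (Protocol article, Sample size):** difference 12.6; SD 18.4 ("90 baseline VISA-P = 50.1 (SD = 18.4")); alpha 0.05; power 0.80; correlation r = 0.5; three equal arms. Powers are from the noncentral F distribution.

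**1. Effect size.** With control at 0 and both HVIGI arms at 12.6, the mean is 8.4 and the SD of the means is √[(8.4² + 4.2² + 4.2²)/3] = √35.28 = 5.940. So f = 5.940/18.4 = 0.3228, which matches the plan, and f² = 0.1042.

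**2. One-way ANOVA.** Noncentrality λ = N·f² = 96 × 0.1042 = 10.0, df 2 and 93, power 80.2%. The plan's 96 is reproduced.

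**3. Source of 75 and 60.** For the between-groups main effect over m visits, λ = N·m·f²/[1 + (m − 1)r].
- m = 2, N = 75: λ = 75 × 2 × 0.1042/1.5 = 10.42, power 81.5%.
- m = 5, N = 60: λ = 60 × 5 × 0.1042/3 = 10.42, power 81.1%.

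Both are the smallest multiples of 3 that reach 80%, so both figures are reproduced exactly. Entering the same f in the within-between interaction formula, λ = N·m·f²/(1 − r), gives 27 and 18. Those are not usable sample sizes either, but they show that 75 and 60 are main-effect figures. The main-effect formula assumes the 12.6-point difference at every visit, including baseline, where randomisation makes the expected difference zero.

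**4. The named interaction, two visits.** This is a one-way ANOVA of change, with SD of change = 18.4 × √[2(1 − r)]. At r = 0.5 this is again 18.4, so f is unchanged: 80.2% power at N = 96, and at N = 75 λ = 75 × 0.1042 = 7.8, power 68.7%.

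**5. The named interaction, five visits.** With 12.6 at all four follow-ups and 0 at baseline, r = 0.5, power is 57% at N = 60; 93 participants are needed for 80%.

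**6. ANCOVA on baseline score.** Residual SD = 18.4 × √(1 − r²) = 15.93 at r = 0.5, so f = 0.3228/0.8660 = 0.3727. At N = 96, λ = 13.3, df 2 and 92, power 90.6%. At N = 75 power is 81.5%.

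**7. Range over the correlation, N = 96.** The documents give only 0.5; the other values are assumptions.

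| r | Time x intervention | ANCOVA on baseline |
|---|---|---|
| 0.3 | 65.0% | 84.0% |
| 0.4 | 72.2% | 86.9% |
| 0.5 | 80.2% | 90.6% |
| 0.6 | 88.6% | 94.6% |
| 0.7 | 95.8% | 98.0% |

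**8. Conditional adjustment.** Simulation of 20,000 trials, 32 per arm, r = 0.5, with the baseline score as the variable tested: change score 80.0%; ANCOVA only if the baseline test is significant 80.5%; ANCOVA always 90.3%. Type I error of the conditional rule was 4.1%.

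**The case against.** The strongest reply is that the plan works on its own terms. Recruitment is set by the one-way calculation (96, raised to 108, 36 per arm in the envelope scheme). The 75 and 60 are described as further, smaller results and are not adopted. At the plan's own correlation, the named interaction reaches 80% at 96, and it does better than that if the correlation is higher. Change-score analysis in a randomised trial is unbiased. All of this stands.

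Three stronger readings are tempting, and the documents do not support them.

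- **That the primary test has only about a third of the power it needs.** A group main effect that averages in a zero baseline difference would have 27% power at 75 and 34% at 96. But the section names the interaction in brackets, so these figures explain why 75 and 60 do not fit; they are not the power of the planned analysis.
- **That the trial is too small because of 75 or 60.** The target does not rest on them.
- **That the conditional ANCOVA biases the primary result.** The sentence that makes ANCOVA conditional sits in a paragraph on demographic data and risk factors and does not name the baseline VISA or VAS score. Even when the rule is applied to that score, simulated type I error was below 5%. Nor is the baseline score ignored: it enters the repeated-measures model every time, but inefficiently.

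What remains is the lost efficiency and the two figures attached to the wrong test.

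**Conclusion.** The point holds as an efficiency loss and a correction of two stated figures; it should be fixed, and no bias is shown. At correlation 0.5 and 96 participants the planned interaction gives up about 10 percentage points of power against baseline-adjusted ANCOVA (80% against 91%). The gap is 19 points at 0.3 and 2 points at 0.7. Below 0.5 the planned test falls under 80% at 96, while ANCOVA stays above it down to at least 0.3. Conditional adjustment recovers almost none of the loss. The 75 gives 69% power for the named two-visit interaction, and the 60 gives 57% for the five-visit one under the pattern assumed above.

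These results assume the same SD of 18.4 at both visits, control at 0 with both HVIGI arms at 12.6, equal arms and the omnibus test at 0.05. They concern VISA-P, the only outcome for which the plan gives a difference and SD.

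**What to change.** - Make the primary analysis an ANCOVA of the 6-month score on arm and baseline score, always fitted. Use the same baseline adjustment for the other visits.
- Drop the baseline significance tests, and remove the wording that makes ANCOVA conditional on them. Baseline characteristics can still be tabulated by arm. Adherence is measured after randomisation and does not replace the baseline score.
- Delete 75 and 60. Alternatively, replace 75 with a newly run baseline-ANCOVA calculation, which at correlation 0.5 needs 73, or 75 with equal arms. That this equals the quoted figure is a coincidence of the correlation: 2/(1 + r) and 1/(1 − r²) are both 1.333 at r = 0.5. It should be reported as a new calculation, not as a relabelling of the one described.

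The cost is wording in the protocol and analysis plan, settled before unblinding. No extra participants, visits or data are needed, and the target of 108 can stand.

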### Roles and responsibilities

The role of the Sponsor (Director of Defence Rehabilitation) is to: “Promote effective professional guidelines and support to medical rehabilitation providers. Develop, promote and co-ordinate the standardisation and delivery of best evidence clinical practice across Defence. To support medical rehabilitation in the operational environment in order to assist in the maintenance of fighting power. To provide an inspectorate role across Defence Medical Rehabilitation. To provide leadership for rehabilitation cadres, including: Rheumatology & Rehabilitation consultant, Sport & Exercise Medicine, Physiotherapy, Exercise Rehabilitation Instruction and other Allied Health Professional groups. Co-ordination, collection and analysis of medical intelligence and data related to rehabilitation.”

As the Director of Defence Rehabilitation (DDR) The Sponsor welcomes this research to further develop the DDR tendinopathy guidelines. The Sponsor can be contacted via email [contact].

Given the nature of this research an independent trial steering committee has not been appointed. An Independent Medical Officer (IMO) has been appointed to act as a point of contact outside of the research team. The IMO is available for patients/participants and staff members who may have any questions or concerns that might not necessitate the significant event reporting process.

The Trial Management Group meets at least quarterly and consists of the authors listed above.

This protocol has been reviewed and approved by the: The Defence Medical Services Research Steering Group, The Surgeon General’s Higher Degree Board, The Dean of the School of Sport, Exercise and Health Sciences, Loughborough University, The Defence Science and Technology Laboratory’s Scientific Assessment Committee, MODREC with acceptance of this approval by LU ethics committee and the MHRA. Amendments suggested by these bodies have been incorporated into this protocol.

### Monitoring

An Independent Data Monitoring Committee (IDMC) has been appointed in accordance with National Research Ethics Service guidance [36] and the DAMOCLES study group recommendations [37]. Members are the clinical research manager of ADMR, the chair of the DMRC Medicines Management Committee, the DMRC Clinical Quality Manager and an Independent statistician. The Chief Investigator will analyse and make available accruing data, the protocol deviation log and significant event reports prior to the IDMC meeting 6 monthly. The ADMR manager will inspect all locked stores containing Case Report Forms and audit transfer to results spreadsheets monthly. As set out in its charter the IDMC makes recommendations to the Sponsor who retains executive decision-making on trial stopping.

